#### Other Study Parameters

Other study parameters used in this study are as follows: (1) comorbidities (Charlson comorbidity index) [32]; (2) complications (Clavien Dindo [33] and nurse-sensitive outcomes [34]); (3) postoperative days (T0=surgery); (4) surgery characteristics (invasiveness, etc) [20]; (5) musical background (excerpt from DMBQ) [30]; (6) age; and (7) presurgery cognitive testing [22] (eg, 6-item cognitive impairment score) [28].

### Treatment Allocation

This study will take the form of an on-off NCT [26]. An on-off NCT takes into account real-world setting limitations of certain intervention types and allocates participant inclusion by alternation. The main reason for this is that MiMiC is a well-researched intervention, whose practical implementation is not suited for randomly selected participants to not participate. On the one hand, musicians will visit the nurses’ station and play music in various rooms around the ward; thus, it is not possible to prevent participants who may be allocated non-MiMiC treatment from hearing the live music. On the other hand, a central tenet of the MiMiC intervention is inclusion and participation, thus “rejecting” patients who would want to participate in music they hear on the ward, on the basis of trial group allocation, goes against the spirit of the intervention.

In contrast, the NCT relies on the randomness of who is scheduled for surgery during a given intervention week but does not exclude any patient from the activity being conducted (listening to live or recorded music). Therefore, the treatment schedule (live music intervention, recorded music active control, and standard care control) will be predetermined months in advance, and the patients included will be offered whichever treatment is occurring during their hospital stay. The patients will, however, be asked for their consent before they are informed which treatment will be offered during their surgery recovery. This will attempt to prevent patients who are initially biased for inclusion based on their affinity to music or not.

### Study Procedures

After patients are recruited to the study, they will be allotted to the treatment occurring during the scheduled postoperative hospital stay. Noninvasive procedures include preoperative cognitive testing (6CIT), postoperative VAS pain ratings, HR, blood pressure, respiration rate, and EEG recording. Invasive procedures include obtaining blood samples, after which the serum will be analyzed in a laboratory for neuroinflammatory markers IL6, NGAL, CRP, and serum TPSO. An example schedule of procedures can be found in Table 1.

### Primary End Point

The main end point, VAS pain ratings, requires patients to subjectively rate their pain on a plastic VAS where they move a tick mark to the desired location on a 0-10 scale [1].

### Secondary End Points

The secondary end points, HR and blood pressure, will be collected from standard equipment on the ward at the time of obtaining VAS pain ratings.

#### Pulmonary Ventilation

Respiration rate and tidal volume have been linked to subjective pain experience in the literature [4]. Therefore, in order to see whether our pain findings extend from subjective to objective physiological measures, we will explore the association between these 2 objective metrics and subjective pain VAS ratings. A wearable biosensor that measures pulmonary ventilation metrics [35] will be placed on the chest of patients with an adhesive sticker and removed at the end of the day.

#### Blood Marker Analysis

One 10-ml vial of blood will be collected per day resulting in a maximum of 5 vials of blood over 5 days. The first sample must be taken before the first assigned intervention. Blood samples will be collected together with standard care insofar as possible. Serum extracted from blood samples will be processed by the Haemoscan lab and evaluated for the presence of 4 markers associated with neuroinflammation (IL6, NGAL, CRP, and serum TPSO; see “Introduction” section).

#### EEG Recordings

As opposed to typical electrode setup with, for example, a cap, the face electrode grids for EEG recording require minimal preparation of skin and are quickly applied. Each morning, the patient’s face will be cleaned and prepared with exfoliating gel, and electrodes will be applied with adhesive tape. The face electrode grid for EEG recordings will remain on the patient from morning until evening, spanning the first and last pain VAS ratings. Actual recordings will occur 4 times a day, in 15-minute increments, coinciding roughly with the times that pain VAS ratings are collected (before intervention, during intervention, 3-hour, and 6-hour postintervention). During the 15-minute EEG recording windows, the patients will be instructed to remain seated or lying doing a consistent activity of their choice, or otherwise as instructed during the assigned treatment.

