Design procedures are chronologically displayed in Figure 1. Preoperative questionnaires will be collected to assess cognitive function (6-item cognitive assessment [6CIT]) [27,28] and musical background (excerpt from the Dutch Musical Background Questionnaire [DMBQ]) [29,30]. Postoperative data collection procedures per day of treatment include pain visual analog scale (VAS) ratings, heart rate (HR), and blood pressure measuring 4 times a day (before, directly after, 3-hour, and 6-hour postintervention). EEG electrodes will be applied once in the morning and 4 EEG recordings will be collected with VAS ratings, HR, and blood pressure (before, during, 3-hour, and 6-hour postintervention). A blood sample will be collected once daily and integrated with standard care as far as possible (eg, if blood is drawn as part of standard care, the sample will be collected from the same needle). A schedule of assessments may be found in Table 1. Daily dosage of pain medication as well as any incidence of delirium (delirium observation screening scale [DOSS]) [31] or POCD will be collected.

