**Postoperative**			
	9 AM	fEEGrid^a^ preparation and placement Respiration biosensor placement Blood vial^b^	10
	10:30 AM	VAS^c^ rating, HR^d^, respiration rate, blood pressure, and start EEG^e^ recording	5
	10:40-11 AM	MiMiC^f^ or recorded music or no intervention VAS rating, HR, respiration rate, blood pressure, and stop EEG recording	20
	2 PM	VAS rating, HR, respiration rate, blood pressure, and EEG recording	15
	5 PM	VAS rating, HR, respiration rate, blood pressure, and EEG recording	15
	5:15 PM	Remove fEEGrid and respiration biosensor	5
	Total	N/A^g^	70

^a^fEEGrid: face electrode grid for EEG recordings.

^b^The blood vial collection will be integrated into standard care as much as possible, thus, the time may not be 9 AM if other blood collection is at a different time.

^c^VAS: visual analog scale.

^d^HR: heart rate.

^e^EEG: electroencephalogram.

^f^MiMiC: Meaningful Music in Healthcare.

^g^N/A: not applicable.

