### Secondary Study Parameters

For metrics that are collected on the same schedule as the VAS (EEG alpha power, delta/alpha power ratio, entropy metrics, HR, respiration rate, and blood pressure), the values per participant will be entered into the same *F* test described for the VAS ratings (as well as correlated with other baseline parameters as described in the “Other Parameters” section). For blood marker metrics that have 2 data collection points, a similar RM ANOVA will be conducted, but with 2 as opposed to 4 measures, and a significant interaction between treatment and time point would indicate whether treatment significantly impacted the amount of the neuroinflammatory blood marker. Categorical incidence metrics (delirium and POCD) will be evaluated with a one-way ANOVA to determine whether treatment impacted these neuroinflammatory-related complications. Delirium and signs of delirium will be perceived using the DOSS. The DOSS is a screening instrument for delirium, consisting of 13 items, and will be filled by a registered nurse during hospital admission until discharge. Nurses have frequent contact with the patients and are in a good position to observe behavior changes 24 hours a day when patients are admitted. The DOSS is already part of a routine in the surgical wards and all registered nurses are already trained. Likewise, scalar pain medication dosage will be averaged over 24-hour periods per patient and entered into a chi-square test to determine whether the dosage was significantly different across the 3 treatment groups. As this is exploratory and serves to inform future hypothesis-directed testing, we will not correct for multiple comparisons.

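### The second EEG recording is made during the session, not on the VAS schedule, so the shared four-point F test cannot separate an acute response to the arm's activity from an effect on neuroinflammation

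*Protocol article*

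**What the plan says.** Study Design in the protocol article takes VAS, heart rate and blood pressure "before, directly after, 3-hour, and 6-hour postintervention". The same section and EEG Recordings both put the second EEG recording inside the session; the latter gives the order as "before intervention, during intervention, 3-hour, and 6-hour postintervention".

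EEG Recordings adds: "Actual recordings will occur 4 times a day, in 15-minute increments, coinciding roughly with the times that pain VAS ratings are collected". During these windows patients stay seated or lying with one consistent activity, "or otherwise as instructed during the assigned treatment". The Abstract says that live-music patients are asked to interact with the musicians and that recorded-music patients listen over headphones.

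The statistical section Secondary Study Parameters opens "For metrics that are collected on the same schedule as the VAS" and lists EEG alpha power, the delta/alpha ratio and entropy among those metrics. All go into the F test used for VAS, and Table 2 repeats this. That test's result of interest is the group by time point interaction (Primary Study Parameters). The end-point list calls the three metrics EEG markers of neuroinflammation, and the Introduction asks whether either music arm mitigates such markers.

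Table 1 has "VAS^c^ rating, HR^d^, respiration rate, blood pressure, and start EEG^e^ recording" at 10:30 AM. The intervention row runs from 10:40 to 11:00 and closes with "respiration rate, blood pressure, and stop EEG recording".

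**The concern.** For VAS, a change just after the session is the effect that the trial is looking for. For an EEG measure read as a marker of neuroinflammation, a change while the music is playing has a rival explanation: the patient is listening or interacting at that moment. The interaction test is an omnibus test, so an arm difference at any single time point can make it significant, including one that has gone by 3 hours.

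What is at stake is how an EEG interaction is read. Without separation of the during-session recording, a transient response could be carried forward as a sign that music mitigates neuroinflammation. The secondary analyses are meant to shape later hypotheses and are not corrected for multiplicity, so the analysis as written has no step that would catch this.

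A smaller issue concerns the first recording. The start time in Table 1 and the 15-minute length in EEG Recordings do not fit together before the session begins.

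**Working it through.** **1. Schedules side by side**

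| Point | VAS, heart rate, blood pressure | EEG |
|---|---|---|
| 1 | before | before |
| 2 | directly after | during |
| 3 | 3 hours after | 3 hours after |
| 4 | 6 hours after | 6 hours after |

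Point 2 differs, so the same-schedule statement is wrong for EEG.

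**2. The article's own figure for this F test**

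Inputs (Power section and Table 3): f = 0.2318206, N = 327, 3 groups, 4 measurements, α = 0.05, no sphericity correction.

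- λ = f² × N = 0.2318206² × 327 = 17.573
- df1 = (3 − 1)(4 − 1) = 6; df2 = (327 − 3)(4 − 1) = 972
- critical F = 2.1079; power = 0.9008

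All agree with Table 3.

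**3. Illustration: a shift at point 2 only**

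Assumed, not in the article: the live arm shifts by d at point 2, the recorded arm by d/2 and controls by 0. There is no arm difference at points 1, 3 and 4. The SD (1 unit) and the correlation ρ are the same at all points; n = 109 per arm.

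- Group deviations at point 2: d/2, 0, −d/2; sum of squares d²/2.
- Removing each arm's own mean over four points leaves a factor 3/4, so the interaction sum of squares is 0.375 d².
- λ = 109 × 0.375 d² / (1 − ρ) = 40.875 d² / (1 − ρ)
- Example, d = 0.5 and ρ = 0.5: λ = 40.875 × 0.25 / 0.5 = 20.44.

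Probability of a significant interaction (noncentral F, df 6 and 972):

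| d (live arm) | ρ = 0.3 | ρ = 0.5 | ρ = 0.7 |
|---|---|---|---|
| 0.1 SD | 0.07 | 0.08 | 0.11 |
| 0.2 SD | 0.165 | 0.22 | 0.36 |
| 0.3 SD | 0.35 | 0.49 | 0.75 |
| 0.5 SD | 0.83 | 0.94 | 0.998 |

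With another pattern (shift in the live arm only, or equal in both music arms) the 0.3 SD row becomes 0.47, 0.63 and 0.88.

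**4. The same test without point 2**

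The three remaining points carry no shift, so λ = 0 and rejection is at the nominal 5%. A simulation with a 0.5 SD shift confined to point 2 in the live arm gave 5.4%. Degrees of freedom become (3 − 1)(3 − 1) = 4 and 324 × 2 = 648. With the article's f and N, power is 0.936. That figure only shows that fewer points need not cost power, because f is held fixed.

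**5. Clock check on the first recording**

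10:30 + 15 minutes = 10:45. The intervention slot opens at 10:40, so 5 of the 15 minutes would fall in it if Table 1 is followed literally. Only 10 minutes precede the slot.

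If the first recording carried one third of the shift (5/15), the three-point test has λ = 109 × (1/2)(d/3)² × (2/3) / (1 − ρ). At d = 0.5 and ρ = 0.5 this is 2.02, and rejection is about 17%. Dropping point 2 would then not be enough by itself.

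**The case against.** The article does not say that alpha power, the delta/alpha ratio or entropy react at once to listening or movement. It shows that activity differs between arms at point 2, not that EEG does. This stands: the acute response has to be labelled an assumption, and at a 0.1 SD shift the effect on the test is slight (7% to 11%).

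A reader might infer that a significant EEG interaction is to be expected even if music does nothing to neuroinflammation. The documents do not support that. Only the activity differs by construction, and in the illustration the result at 0.3 SD and correlation 0.5 is close to a coin toss.

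A reader might also infer that the baseline is contaminated. Study Procedures calls Table 1 an example schedule, and recordings match the VAS times only roughly. The 20-minute intervention row also holds measurements, while the music lasts 15 minutes, so the onset of the music is not fixed. Both descriptions of the first recording place it before the intervention. What remains is a timing mismatch to reconcile.

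Movement is partly handled by the seated-or-lying instruction, although treatment is excepted from it. EEG is exploratory, and blood markers and delirium or cognitive decline address the same objective. The explicit reading of an interaction as a treatment impact is written for the blood markers, not for EEG.

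None of this removes the core: the second EEG recording is not at the VAS time point, and an interaction that includes it has two explanations.

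**Conclusion.** The concern holds in a limited form. The article misstates the EEG schedule in its analysis section. As a result, a significant four-point EEG interaction cannot by itself support mitigation of neuroinflammation.

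The size depends on an acute response that the article does not quantify. Under the assumed pattern, rejection without any lasting effect is about 16.5% to 36% at 0.2 SD, 35% to 75% at 0.3 SD and 83% to 99.8% at 0.5 SD, for correlations 0.3 to 0.7. It is about 5% when point 2 is left out. These are illustrations, not forecasts.

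It would go too far to say that the secondary objective will be answered wrongly. EEG is one of several strands, and all of them are exploratory. The baseline overlap, at most 5 of 15 minutes, is possible on a literal reading of Table 1 but not established. The primary VAS analysis and the sample size are untouched.

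**What to change.** - In Secondary Study Parameters and Table 2, stop describing EEG as sharing the VAS schedule and analysis. Test the EEG neuroinflammation markers on the before, 3-hour and 6-hour recordings.
- Report the during-session recording separately, labelled as an acute response.
- State that the EEG baseline uses only signal from before the session starts.
- Reconcile the 15-minute recording length in EEG Recordings with the 10:30 and 10:40 entries in Table 1.

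All four recordings are kept and no new data are needed. The electrodes are in place from 9 AM in the example schedule, so a timing correction is small. The cost is one fewer time point in an exploratory secondary test. Data collection is expected to run to 2026, so the change can still be specified before the analysis.

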**Methods:**

This intervention study will compare subjective postsurgical pain ratings among 3 groups: live music intervention, recorded music intervention, and standard care control. The design will take the form of an on-off nonrandomized controlled trial. Adult patients undergoing elective surgery will be invited to participate. The intervention is a daily music session of up to 30 minutes for a maximum of 5 days. The live music intervention group is visited by professional musicians once a day for 15 minutes and will be asked to interact. The recorded music active control intervention group receives 15 minutes of preselected music over headphones. The do-nothing group receives typical postsurgical care that does not include music.

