### Primary Study Parameters

Pain ratings will be collected 4 times a day with a VAS. VAS mean and SD will be reported, and box plots, histograms as well as *P* values for Kolmogorov-Smirnov tests will be evaluated for normality of distribution. A univariate, one-way repeated measures (RM) ANOVA will be conducted with factors group (live music intervention, recorded music active control, and standard care control) by time points (1, 2, 3, 4). The α significance threshold will be .05. The result of interest is the significance of the training×time point interaction, that is, whether the course of the data across time points was altered by the training type. Data are planned with 4 time points; in case of up to 2 missing time points, data will be interpolated [37]. Cases with more than 2 missing time points will be excluded from the analysis. Alternatively, if the residuals of the ANOVA are not normally distributed, a similar Kruskal-Wallis one-way ANOVA will be conducted.

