## Discussion

### Principal Findings

Previous studies have shown that postoperative pain management can be supplemented with music intervention. Yet, little is known about the benefits of live versus recorded music, or what physiological mechanisms may be mitigating pain perception as a response to listening to music. This NCT will compare the MiMiC live music intervention with listening to recorded music and care-as-usual. The primary objective is to see whether pain VAS ratings differ across the 3 conditions, and the secondary objective is to see whether postoperative neuroinflammation is reduced as a response to listening to music.

The strength of this study is the inclusion of preoperative assessments to establish some baseline characteristics of patients. First, the preoperative musical background questionnaire (selected items from [30]) assesses the estimated weekly hours of music listening as well as listening preferences for musical genre and whether or how the participant is musically trained. This provides us the opportunity to analyze how the extent of musical exposure may affect the primary outcome (pain VAS) of the intervention; depending on the strength of these findings, we may be able to even help inform future music interventions according to preoperative musical habits. Second, the preoperative cognitive assessment (6CIT) [28] serves as an important baseline for several secondary outcomes that may help to account for variability among the 3 intervention arms that otherwise might be attributed to the treatment. Specifically, the 6CIT will inform the interpretation of the postoperative cognitive status, and it may predict alpha power in EEG recording [22] that in turn may be linked to delirium [23,24]. If this proves to be the case, the preoperative cognitive status might be investigated in the future as a method to inform more at-risk patients who could especially benefit from supplementary nonpharmacological interventions [41] such as live or recorded music [42].

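### The activity rule for the EEG windows leaves self-chosen music open to standard-care patients in the session slot, although the control is defined as music-free

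*Protocol article*

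**What the plan says.** Three places in the protocol article bear on this.

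- **Control definition (Abstract, Methods):** "The do-nothing group receives typical postsurgical care that does not include music".
- **Session slot (Table 1, 10:40-11 AM):** the entry offers live music "or recorded music or no intervention". The pain rating is listed after the intervention in that slot, and the EEG recording is stopped there.
- **Behaviour in the recording windows (EEG Recordings):** there are four 15-minute recordings a day, "coinciding roughly with the times that pain VAS ratings are collected", and during them patients are "instructed to remain seated or lying doing a consistent activity of their choice, or otherwise as instructed during the assigned treatment".

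The rule neither names music nor excludes it. The only information on music use is the preoperative questionnaire, which "assesses the estimated weekly hours of music listening" together with genre preference and training (Principal Findings). The article describes no record of music heard during the hospital stay.

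**The concern.** A standard-care patient who listens to their own music while seated or lying satisfies the activity rule. In the session slot that patient would receive something close to the recorded-music treatment and would then give the post-intervention rating. That works against a control defined by the absence of music.

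The article gives up randomisation partly because patients allocated to other treatments could not be kept from hearing the live music (Treatment Allocation). It also cites earlier work in which recorded music reduced postsurgical pain (Introduction). On its own reasoning, then, own music in the control session slot could matter. At stake are the two contrasts with control and, through them, the group by time interaction. Nothing described in the article would let the analyst see afterwards whether this had happened.

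A second, smaller matter is that letting patients choose the activity in the before, 3-hour and 6-hour recordings leaves task and eye state uncontrolled when alpha power is measured.

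**Working it through.** **1. Which rule governs the control patient in the session slot?** The activity rule has two parts: free choice, and an override where the assigned treatment instructs otherwise. For the music arms the override is the session itself. For standard care, Table 1 says no intervention, and no other section of the article tells these patients what to do in the slot. As written, free choice governs. The Abstract limits what the care includes; it does not limit what the patient may choose to do.

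**2. Which ratings can be affected?** Table 1 lists the events in this order.

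| Time | Order listed | Rule differs between arms? |
|---|---|---|
| 10:30 AM | rating, then EEG start | No |
| 10:40-11 AM | intervention or none, then rating, then EEG stop | Yes |
| 2 PM | rating, then EEG | No |
| 5 PM | rating, then EEG | No |

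Only in the session slot does the rule differ by arm, and only there is the rating listed after the possible exposure.

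**3. The plan's own sample size.** Inputs from Power and Table 3: partial η² = 0.051, 3 groups, 4 measurements, ε = 1, power 0.9. The test is the interaction ("The result of interest is the significance of the training×time point interaction"), and "The α significance threshold will be .05".

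- f = √(0.051/0.949) = 0.23182
- df = (3−1)(4−1) = 6 and (327−3)(4−1) = 972
- λ = f² × N = 0.23182² × 327 = 17.573
- critical F = 2.1079, power = 0.9008

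These match Table 3, and 327 is the smallest total divisible by 3 that reaches 0.90. No stated figure is wrong.

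**4. Illustration of dilution.** The following are assumptions, not figures from the article. A share c of controls obtains the full recorded-music effect. Recorded music has r times the live effect. The stated f holds at c = 0. The interaction scales with the spread of the three group effects.

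- Recorded versus control is multiplied by (r − cr)/r = 1 − c.
- Live versus control is multiplied by 1 − cr.
- f(c) = f × √[Var(cr, r, 1)/Var(0, r, 1)].

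Example with r = 0.5 and c = 0.20: Var(0.1, 0.5, 1) = 0.1356 and Var(0, 0.5, 1) = 0.1667. The ratio is 0.813, so f = 0.2318 × 0.902 = 0.2091 and power at 327 is 0.82.

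| c | Recorded vs control | Live vs control, r = 0.5 | Power at 327: r = 0 | r = 0.5 | r = 1 |
|---|---|---|---|---|---|
| 10% | 0.90 | 0.95 | 0.90 | 0.86 | 0.82 |
| 20% | 0.80 | 0.90 | 0.90 | 0.82 | 0.70 |
| 30% | 0.70 | 0.85 | 0.90 | 0.77 | 0.56 |

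Live versus recorded does not contain c at all.

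**The case against.** The strongest reply is that the rule is an EEG instruction about keeping still, set within arms already defined. Standard care is one of the three treatments, so the override clause could cover control patients too. What they are told at the bedside may sit in the full protocol, which an article condenses. This stands to the extent that contamination is possible, not shown. It does not dispose of the point: the article states a positive rule, and that rule permits what its control definition excludes.

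A reader might go further and infer that the no-music comparison is contaminated at every rated time point, or that the later ratings cannot show whether a session's effect lasts. The article does not support this. Nowhere does it say that control patients will listen to music. The rule is identical across arms in the before, 3-hour and 6-hour windows, and Table 1 lists the rating before the EEG at each of those times. Nor is there support for the inference that joining a music study makes own music more likely. That is conjecture, and patients consent before learning their treatment (Treatment Allocation).

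It is also fair to say that own music may be part of ordinary hospital life, and that enforced silent rest would move the comparator away from care-as-usual. This stands as an argument against banning television or other distraction from controls. It does not justify leaving music open, because the article itself describes the control as care without music.

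Finally, music heard between the windows remains uncontrolled under any rule for the windows. That is true, and it is the reason for recording it.

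**Conclusion.** The point holds in a limited form. Self-chosen music is open to standard-care patients in the 10:40-11 AM slot, immediately before the post-intervention rating, and this conflicts with the music-free definition of the control. It can shrink both contrasts with control. How far is unknown: the article gives no share of patients, and the table above rests on assumed values of c and r and on own music working as well as the recorded intervention. If recorded music has no effect, nothing is lost.

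The live-versus-recorded comparison is untouched, and the sample size of 327 (360 with dropout) is not in error. In the other three windows the concern is mainly extra variation in alpha power from a self-chosen task and eye state. It is a lesser matter, since those analyses are declared exploratory.

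**What to change.** Make three small changes, starting with the rule in EEG Recordings.

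1. Restrict the activity to a consistent quiet one other than listening to music. Apply this to every window outside an assigned music session, including the control arm's 10:40-11 AM slot.
2. Use one uniform activity and one eye state for the before, 3-hour and 6-hour EEG recordings in all arms.
3. Add a daily tick box for self-chosen music, so that it can be described by arm.

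Do not bar television or other ordinary distraction from control patients in the session slot, since that would change the usual-care comparator.

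The cost is one amended instruction and one form item. Patients forgo their own music for at most about an hour a day (4 windows × 15 minutes = 60 minutes). The sample size does not change. The article reports 5 participants recruited at submission. Bringing the change in at the start of a 29-day block would keep the three arms within each block under the same rule.
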